**Table 11. List of Sick Cell Related or Right Heart Catheterization Related Adverse Events**

| Sickle Cell Disease                                                                                                         |                                     |                            |
|------------------------------------------------------------------------------------------------------------------------------------|-------------------------------------|----------------------------|
| Acute chest syndrome                                                                                                               | Ileus                               | Renal failure              |
| Amenorrhea                                                                                                                         | Infection, other bacterial          | Renal insufficiency        |
| Anemia (severe)                                                                                                                    | Infection, pneumococcal             | Renal papillary necrosis   |
| Aplastic crisis                                                                                                                    | Infection, line                     | Retinopathy                |
| Avascular necrosis of hip/shoulder                                                                                                 | Infection, viral                    | Rhabdomyolysis             |
| Bacteremia                                                                                                                         | Jaundice                            | Seizure                    |
| Bone infarction                                                                                                                    | Meningitis                          | Septicemia                 |
| Cardiomegaly                                                                                                                       | Nephropathy                         | Silent infarct             |
| Cholecystitis                                                                                                                      | Osteomyelitis                       | Skin ulcer                 |
| Cognitive dysfunction                                                                                                              | Pain, back                          | Splenic sequestration      |
| Decreased renal function                                                                                                           | Pain, chest                         | Splenic sequestration      |
| Decreased lung function                                                                                                            | Pain, joint                         | Splenomegaly               |
| Delayed growth/puberty                                                                                                             | Pain, long bone                     | Transfusion, unanticipated |
| Depression                                                                                                                         | Pain, severe abdominal              | Vaso-occlusive pain        |
| Electrolyte imbalance                                                                                                              | Pain, sternal or rib                |                            |
| Elevated serum transaminases                                                                                                       | Proteinuria                         |                            |
| Fever                                                                                                                              | Pneumonia                           |                            |
| Hand-foot syndrome/dactylitis                                                                                                      | Pulmonary embolism                  |                            |
| Hematuria                                                                                                                          | Pulmonary hypertension              |                            |
| Hemiplegia                                                                                                                         | Pulmonary infiltrate on chest x-ray |                            |
| Hepatic sequestration                                                                                                              | Pyelonephritis                      |                            |
| Hepatomegaly                                                                                                                       |                                     |                            |
| Hospitalization >24 hours for sickle cell related events                                                                           |                                     |                            |
| Hypersplenism                                                                                                                      |                                     |                            |
| Hypertension                                                                                                                       |                                     |                            |
| Hypoxemia (PO 2 < 65mm Hg)                                                                                              |                                     |                            |
| Catheterization Procedure                                                                                                   |                                     |                            |
| Arterial puncture                                                                                                                  | Hematoma                            | Vasovagal reaction         |
| Cardiovascular symptoms occurring more than 24 hours after admin of pharmacologic agents (e.g. prostacyclin, nitric oxide, oxygen) | Transient arrhythmia                |                            |
| Chest or extremity discomfort                                                                                                      | Non-sustained hypotension           |                            |

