### **13.6.2 IND Safety Reporting to the FDA**

Because this study will be conducted under an IND, U.S. Government regulations 21CFR, Part 312.32 require the issuance of an IND Safety Report to the Food and Drug Administration (FDA) for all “serious” adverse events that are “unexpected” and for which there is a “reasonable possibility that the experience may have been caused by the drug.” Such serious events that are characterized as fatal or life-threatening must be reported to the FDA within 7 calendar days of the sponsor’s initial receipt of the information, whereas non-fatal and non-life threatening events must be reported within 15 calendar days.

The list in Table 11 identifies potentially serious adverse events that are “expected” based on the underlying disease, sickle cell anemia, or on the right heart catheterization procedure. Section 13.7.2 includes additional expected SAEs based on PH and study procedures. No expedited IND Safety Report is required if the event is considered to be expected based either on the sildenafil product label, the underlying disease states (i.e., PH or sickle cell disease), or the study procedures. Additionally, a serious adverse event requires an expedited report to the FDA only if it is considered to be at least possibly related to study drug.

The Product Safety Team will issue IND Safety Reports to NHLBI for all unexpected, serious adverse events that are believed to be at least possibly related to study drug. In compliance with FDA and National Institutes of Health (NIH) regulations, the Product Safety Team will prepare a collaborative report of these qualifying SAEs using the current version of the FDA MedWatch reporting form. The form will be sent to NHLBI for review and submission to the FDA. When an SAE requiring an IND Safety Report has not resolved by the report deadline, NHLBI will send the report to the FDA, and the Product Safety Team will work with the CI’s to gather follow-up reports on the event.

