### **13.7 Reporting of Adverse Events to the IRB**

#### **13.7.1 Expected AEs that Require no IRB Reporting**

The following expected adverse events will be listed in the consent approved by IRB and will not be reported to IRB.

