#### **Cardiology**

- Vasovagal symptoms during placement of intravascular or arterial catheters or during blood draw.
- Cardiovascular symptoms occurring less than 24 hours after administration of pharmacologic agents (e.g., nitric oxide, oxygen) during cardiac catheterization studies

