#### **Hematology (Sickle Cell Anemia)**

- Priapism requiring medical or surgical intervention
- Acute chest syndrome/pneumonia requiring simple or exchange transfusion, admission and antibiotic therapy (not mechanical ventilation)
- Infections from bacteria, viruses, protozoa and fungi requiring vasopressor support or hospital admission
- Avascular necrosis of the femoral head requiring surgical intervention

- Bleeding requiring transfusion
- Major bleeding complication including intracerebral hemorrhage, stroke or GI bleed
- Sustained thrombocytopenia or neutropenia
- New leg ulcers requiring surgical intervention
- Greater than two admissions for vaso-occlusive crisis per week for two sequential weeks
- Retinal detachment or vitreous bleeding
- Pulmonary embolism
- All hospitalizations for medical indications (with the exception of hospitalizations for vaso-occlusive crises – per Section 13.7.1)

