## **13.8 Reporting of Serious Safety Issues to the DSMB; Suspension Guidelines**

Serious safety issues that arise in this study will be brought to the attention of the Data and Safety Monitoring Board (DSMB), which will make recommendations to the National Heart, Lung, and Blood Institute (NHLBI) regarding possible suspension or termination of the study. The NHLBI will consider the DSMB's recommendations, determine an appropriate action and notify the Data Coordinating Center (DCC). The DCC will notify all participating investigators, who will implement the actions directed by the NHLBI. This section defines "serious safety issues" and describes procedures for bringing them to the attention of the DSMB.

The DCC or PI will make the following types of reports that can alert the DSMB to a potential safety issue:

- Ad hoc reports of unexpected serious adverse events and those serious adverse events associated with major bleeding that are made within 7 or 15 calendar days, as specified in subsequent paragraphs.

- Reports of quarterly statistical analyses of all serious adverse events. The DCC will make such analyses quarterly, but files a report to the DSMB only when analyses indicate that a safety issue has arisen, as defined by the “alert” criteria.
- Reports of semi-annual DCC analyses of all adverse events and of adverse clinical laboratory trends. These reports will highlight any safety issues revealed by the analyses that meet the “alert” criteria.

The DCC will submit the DSMB report to the Chair of the DSMB Subcommittee appointed to monitor this study and to the NHLBI Project Officer and will submit the unexpected SAE report to all study investigators. Each CI will submit the unexpected SAE report to the local Institutional Review Board (IRB) and other local authorities in accordance with the institution’s regulations.

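### Table 11 and Section 13.7.1 set the 24-hour limit for expected cardiovascular symptoms after catheterisation agents in opposite directions, and the Table 11 version has no upper limit

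*Protocol*

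**What the plan says.** Section 13.6.2 gives Table 11 its role: "The list in Table 11 identifies potentially serious adverse events that are" to be treated as expected, because of either sickle cell disease or the right heart catheterisation. It then sets the consequence: "No expedited IND Safety Report is required if the event is considered to be expected". The grounds it accepts for expectedness are the drug's label, the diseases themselves (PH or sickle cell disease) and the trial's own procedures.

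Under its catheterisation heading, Table 11 includes "Cardiovascular symptoms occurring more than 24 hours after admin of pharmacologic agents", with prostacyclin, nitric oxide and oxygen as examples. No upper time limit is given.

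Section 13.7.1 is a separate list with its own consequence: "The following expected adverse events will be listed in the consent approved by IRB and will not be reported to IRB". Its cardiology part includes "Cardiovascular symptoms occurring less than 24 hours after administration of pharmacologic agents", with nitric oxide and oxygen as examples, during cardiac catheterisation studies.

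Expectedness also governs one DSMB route. Section 13.8 provides for "Ad hoc reports of unexpected serious adverse events and those serious adverse events associated with major bleeding" within 7 or 15 calendar days, and Table 12 requires an alert for every unexpected SAE.

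**The concern.** The two entries share the event, the 24-hour cut-off and two example agents, and differ in the direction of the inequality. An event expected because of a procedure would normally lie close to that procedure. Table 11 instead starts the expectation after 24 hours and never ends it.

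Catheterisation comes before randomisation in the TRV ≥ 3.0 m/s stratum (Sections 4.4.2.4 and 6). A window opening 24 hours after the baseline challenge therefore covers essentially the whole 16 weeks of blinded treatment. What is at stake is whether a serious cardiovascular event possibly related to study drug, occurring well after the procedure, reaches the FDA and the DSMB promptly or only through routine channels. Section 12.3.2.3 itself records post-marketing infarction, sudden cardiac death and ventricular arrhythmia in temporal association with sildenafil, so this is not a remote class of event for this drug.

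**Working it through.** The main check is a comparison of text. One short calculation shows how much the threshold-based SAE route can replace.

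**1. The two entries side by side**

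| | Table 11 (Section 13.6.2) | Section 13.7.1 |
|---|---|---|
| Event | cardiovascular symptoms | cardiovascular symptoms |
| Time after agent | more than 24 h, no upper limit | less than 24 h |
| Example agents | prostacyclin, nitric oxide, oxygen | nitric oxide, oxygen |
| Consequence of being listed | no expedited IND Safety Report | no IRB report |

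**2. Do the neighbouring entries agree?** Table 11 has six other catheterisation entries: arterial puncture, haematoma, vasovagal reaction, transient arrhythmia, chest or extremity discomfort, and non-sustained hypotension. All six also appear in the pulmonary artery catheterisation part of 13.7.1. Only the cardiovascular item differs.

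**3. Is there another procedure-linked window?** Section 13.7.2, which 13.6.2 describes as holding additional expected SAEs, lists myocardial infarction or a neurological event during catheterisation or within 24 hours after it. That window is bounded and close to the procedure, unlike the one in Table 11. Table 11 also names prostacyclin, which is not in the Table 2 challenge (inhaled NO and oral sildenafil). The text may have been carried over from elsewhere, but that is an inference.

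**4. Tracing an SAE under the literal text.** Take a serious cardiovascular event at week 12 in a catheterised subject, judged possibly related to study drug and not otherwise expected.

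| Route | Depends on expectedness? | Result if classed as expected |
|---|---|---|
| SAE report to DCC by end of next business day (13.6.1) | no | still made |
| Expedited IND Safety Report, 7 or 15 days (13.6.2) | yes | not required |
| Ad hoc DSMB notice, 7 or 15 days (13.8, Table 12) | yes, except serious bleeding | not required |
| Expedited IRB report of medical hospitalisation (13.7.2) | no | still made |
| Quarterly SAE analysis (13.8.1) | no | analysed; reported only if p < 0.01 with a higher rate on active drug |
| Semi-annual report to DSMB (13.8.2) | no | still made; only the alert needs p < 0.01 |

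The IRB row rests on the 13.7.2 entry "All hospitalizations for medical indications (with the exception of hospitalizations for vaso-occlusive crises". Two routes are lost: the expedited IND report and the ad hoc DSMB notice.

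**5. What the quarterly SAE threshold requires.** With n subjects per arm, a affected on sildenafil and none on placebo, the two-sided Fisher p-value is 2 × C(n, a) / C(2n, a). Inputs are n = 66 per arm (Section 11.6) and the critical value 0.01 (Table 12).

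- 7 versus 0: p = 0.013, no report.
- 8 versus 0: p = 0.006, report.
- With one placebo subject affected, 9 versus 1 gives p = 0.017 and 10 versus 1 gives p = 0.009.

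With 33 per arm, 8 versus 0 is again the first split below 0.01 (7 versus 0 gives 0.011; 8 versus 0 gives 0.005). The quarterly test is therefore not a substitute for single-case reporting.

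**6. Who can be affected.** Section 6 sets a minimum of 64 subjects with TRV ≥ 3.0 m/s out of 132 randomised: 64 / 132 = 48%. This counts subjects to whom the entry could apply. It does not count events or missed reports.

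**The case against.** **The lists serve different recipients.** Table 11 concerns expectedness for the FDA; 13.7.1 concerns what need not go to the IRB. The two entries can therefore stand together logically. This stands, so it would be too strong to call them incompatible. It does not explain why an expectation based on a procedure should begin after 24 hours and have no end.

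**The late reading is not automatic.** The entry sits under a catheterisation heading and speaks of symptoms. Under 13.6.1 the Product Safety Team, including the medical monitor or a physician designee, decides expectedness case by case. Classing a week-12 infarction as procedure-expected would take an odd judgement. This also stands: the text permits the reading but does not compel it.

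**Other routes remain.** A reader might infer that a late cardiovascular signal would go unreported until a statistical threshold is crossed. The protocol does not support that. The DCC, IRB and semi-annual DSMB routes traced above do not depend on the threshold, and 13.10.1 adds a safety report before each scheduled DSMB meeting. The threshold limits only the quarterly SAE report and the alert flag in the semi-annual report.

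**13.7.1 does not exempt late events.** A reader might also place the late exemption there. That section exempts early events, and only from IRB reporting. The late exemption comes from Table 11 read with 13.6.2.

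**The marginal effect may be small.** Section 13.6.2 also treats events as expected on the basis of the product label or the underlying disease. Table 11 already lists chest pain, hypertension and pulmonary embolism under sickle cell disease. The label is not in the protocol, so some cardiovascular events might be expected even after correction. Events judged unrelated to study drug need no IND report in any case.

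**Conclusion.** The inconsistency is real and should be corrected. Table 11 and Section 13.7.1 give opposite directions for the same 24-hour limit, the protocol offers no reason, and the neighbouring entries and the window in 13.7.2 suggest an error rather than a deliberate distinction.

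The consequence is limited but specific. Read literally, Table 11 with 13.6.2 allows a later serious cardiovascular event in a catheterised subject to skip the expedited IND Safety Report and the ad hoc DSMB notice for unexpected SAEs, even if possibly related to study drug. The stratum concerned is planned at a minimum of 64 of 132 subjects. The number of reports affected cannot be determined, because the protocol gives neither a cardiovascular event rate nor the content of the product label.

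This conclusion assumes that the Product Safety Team applies Table 11 as written and that no other basis already makes the event expected. The point does not touch the primary endpoint, the analysis or the randomised comparison.

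**What to change.** Reconcile the Table 11 entry with Section 13.7.1 so that both state the same bounded time window after the catheterisation agents. The sponsor has to decide and state which window is intended.

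Add one sentence to 13.6.2: cardiovascular SAEs outside that window are not expected on the basis of the procedure, and are judged on the other bases that section already allows (product label, underlying disease). Judging late events against the study drug alone would go further than needed, because it would drop the underlying-disease basis and so change reporting policy.

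The cost is one table cell and one sentence, and possibly a few more expedited reports. Design, sample size and analysis are unaffected.

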### **13.6.3 Safety Reporting in the United Kingdom**

Reporting SAEs and of suspect, unexpected, serious adverse reactions (SUSARs) will be conducted in compliance with the European Directive 2001/20/EC.

### **13.7 Reporting of Adverse Events to the IRB**

#### **13.7.1 Expected AEs that Require no IRB Reporting**

The following expected adverse events will be listed in the consent approved by IRB and will not be reported to IRB.

#### **Cardiology**

- Vasovagal symptoms during placement of intravascular or arterial catheters or during blood draw.
- Cardiovascular symptoms occurring less than 24 hours after administration of pharmacologic agents (e.g., nitric oxide, oxygen) during cardiac catheterization studies

#### **Pulmonary Artery Catheterization**

- Transient arrhythmia
- Chest or extremity discomfort
- Vasovagal reaction
- Non-sustained hypotension
- Hematoma
- Arterial puncture
- Conduction abnormalities or atrial/ventricular arrhythmias occurring cardiac catheterization study not requiring pacing or cardioversion/defibrillation.
- Pericardial effusion following diagnostic/research cardiac catheterization study not requiring treatment
- Pneumothorax following diagnostic/research cardiac catheterization (left ventricular puncture) not requiring treatment

#### **6-minute Walk**

- Shortness of breath
- Dizziness
- Headache

- Transient arrhythmia
- Accidental injury sustained from falling not requiring medical evaluation
- Chest or extremity discomfort
- Vasovagal reaction
- Non-sustained hypotension
- Atrial/ventricular arrhythmias occurring during study not requiring pacing or cardioversion/defibrillation.
- Accidental injury sustained from falling that requires medical evaluation
- Chest or extremity discomfort requiring treatment
- Sustained hypotension requiring treatment

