### 9.2.3 6-Minute Walk

The 6MW will be performed in accordance with standard practice. Briefly, site personnel will discuss the 6MW test with each patient, and will then allow each patient to complete one practice walk before the Screening 6MW. The practice walk is not required if the patient has completed a documented (in the medical record) 6MW within 3 months of the Screening 6MW. The subject will be encouraged to walk as fast as possible during the preliminary instructions. However, once the walk begins the technician may not provide additional encouragement. Distance walked, Borg dyspnea index, NYHA functional class, and oxygen saturation will be determined (see Appendix D). Once the practice walk is completed, the site personnel will conduct the actual Screening 6MW  $\geq 2$  hours after the practice walk. Upon enrollment into the MIT, at least one additional 6MW test will be completed with each patient prior to Randomization. No additional practice walks will be conducted during the MIT.

The 6MW test performed at baseline must satisfy the following requirements:

- The 6MW test #2 distance should be within 15% of 6MW test #1 distance or a third test is required (6MW test #3). If screening and baseline 6MWs take place on the same day, the 6MW test #1 and 6MW test #2 must be done at least 2 hours apart.
- The 6MW test #3 distance should be within 15% of 6MW test #2 distance or the subject cannot be included in the study. The 6MW test #2 and #3 must be done at least 2 hours apart.
- For the subjects treated with long-term oxygen therapy, the walk test should be performed without supplemental oxygen. If interruption of the oxygen supply is deemed as unsafe and it is required during the baseline 6MW, follow-up 6MWs must be conducted at the same flow rate.

During follow-up visits 6MW tests should be performed on peak study medication dose i.e. 1-2 hours after study medication intake.

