### **Sildenafil**

- Hypotension requiring admission or fluid resuscitation
- Visual changes requiring discontinuation of therapy or ophthalmologic evaluation
- Hypotension that requires vasopressor support
- Priapism requiring exchange transfusion or surgical intervention

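### Sections 13.7.1 and 13.7.2 give opposite IRB-reporting instructions for treated hypotension at a post-dose 6-minute walk, and the walk list's severity qualifiers separate nothing

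*Protocol*

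**What the plan says.** Protocol section 13.7.1 states that the expected events it lists "will be listed in the consent approved by IRB and will not be reported to IRB". Its 6-minute Walk list has 12 items. The last three are "Accidental injury sustained from falling that requires medical evaluation", "Chest or extremity discomfort requiring treatment" and "Sustained hypotension requiring treatment". The milder counterparts are in the same list: "Accidental injury sustained from falling not requiring medical evaluation", chest or extremity discomfort without a qualifier, and non-sustained hypotension. Under the Sildenafil heading of the same section, hypotension is exempt only if it is asymptomatic.

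Section 13.7.2 lists serious events that go to the local IRB within 7 days (death or life-threatening) or 15 days (other serious). Its Sildenafil list includes "Hypotension requiring admission or fluid resuscitation" and, as a separate item, hypotension needing vasopressors. Its Hematology list adds medical hospitalizations other than those for vaso-occlusive crisis, and cites 13.7.1 for that exception. It has no heading for the 6-minute walk.

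Section 9.2.3 fixes the timing: "During follow-up visits 6MW tests should be performed on peak study medication dose i.e. 1-2 hours after study medication intake". Section 8 names hypotension among the drug's potential adverse events.

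**The concern.** A subject who becomes hypotensive at a follow-up walk and is given fluids meets the walk item in 13.7.1 and the sildenafil item in 13.7.2. One section tells the site not to report and the other sets an expedited deadline. The headings do not settle the matter. The walk is deliberately timed to the drug's peak, and the site is blinded to treatment, so it cannot reliably assign the event to the procedure rather than the drug.

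Sites may therefore handle the same event differently, and a site that follows the walk list would not send its IRB an individual report of a treated hypotensive event shortly after dosing. For falls and discomfort the problem is a different one: the list appears to grade by severity but exempts both grades.

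**Working it through.** There is no sample size, power or alpha figure to reproduce. The check is a comparison of text, with one small calculation on the DSMB screen.

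**Step 1. Set the walk pairs beside 13.7.2.**

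| Event at a walk | Milder form exempt in 13.7.1? | More severe form exempt in 13.7.1? | Matching item in 13.7.2? |
|---|---|---|---|
| Hypotension | Yes (non-sustained) | Yes (sustained and treated) | Yes: admission, fluids or vasopressor |
| Fall injury | Yes (no medical evaluation needed) | Yes (medical evaluation needed) | Only through hospitalization |
| Chest or extremity discomfort | Yes (unqualified) | Yes (treated) | Only through hospitalization |

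The direct contradiction is in the first row. In the other two rows the fault lies within 13.7.1, where the qualifier makes no difference to reporting. Three of 12 items are involved: two require treatment and one requires medical evaluation.

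**Step 2. Look for a precedence rule.** There is none. Where the protocol did intend a 13.7.1 exemption to survive 13.7.2, it said so: the hospitalization item in 13.7.2 excepts vaso-occlusive admissions and cites 13.7.1. Walk hypotension has no such exception.

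**Step 3. Compare with the other headings.** For catheterization, severity pairs are split between the sections. Arrhythmia without pacing or cardioversion, and pericardial effusion or pneumothorax without treatment, are exempt; the forms needing intervention are expedited. The walk pairs are not split. This is consistent with the more severe walk items having been placed in the wrong list, but the protocol does not say so.

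**Step 4. Check whether 13.7.1 is for non-serious events only.** It is not. It exempts vaso-occlusive crisis with hospital admission, and inpatient hospitalization makes an event serious under section 13.2.2.

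**Step 5. Check the other reporting routes.**

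- Adverse events are recorded on the case report form (13.2.1). Serious ones reach the coordinating center by the end of the next business day (13.6.1).
- Sections 13.6 and 13.6.1 make IRB reporting subject to section 13.7 and also to each IRB's own requirements.
- Under 13.6.2 no expedited FDA report is required for an event expected from the label, the disease or the study procedures. Hypotension may fall there, given section 8; the label itself is not at hand.
- Ad hoc DSMB reports (13.8) cover unexpected serious events and serious bleeding. Other serious events are screened quarterly by Fisher's exact test with an alert at p < 0.01 (Table 12).

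For the last route, take 66 subjects per arm (section 11.6), a cases on sildenafil and none on placebo. The two-sided p is 2 × C(66, a) / C(132, a):

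- a = 7: p = 0.0132, no alert.
- a = 8: p = 0.0062, alert.
- With one placebo case, 10 sildenafil cases are needed (p = 0.0087).

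This illustration assumes full enrollment. The actual screen pools cases by highest-level MedDRA term, so other events in the same class count too. It detects an imbalance between arms and does not replace an individual report.

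**The case against.** The strongest answer is that the two sections are tiers: 13.7.1 exempts a general form and 13.7.2 catches a worse one. There is support for this. Femoral-head necrosis and new leg ulcers are exempt, but expedited if they need surgery. Treatable infections are exempt, but expedited with admission or vasopressors. Sustained bronchospasm at lung-function testing is exempt, but expedited if it leads to mechanical ventilation. Read that way, treated walk hypotension is exempt until it needs admission, fluids or a vasopressor. The reading is workable, and the precedence sentence proposed here would write it down. It is nowhere stated, however, and it does not explain why one list exempts fall injury both with and without a need for medical evaluation.

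Three stronger readings may tempt a reader, and the protocol does not support them.

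- *All three walk items contradict the expedited list.* Section 13.7.2 has no item for fall injury or for chest or extremity discomfort. Those two conflict only on hospitalization.
- *Drug-related hypotension could go unreported altogether.* The exemption reaches individual IRB reports only. The routes in step 5 remain, and 13.7.2 sends serious events it does not list to local IRBs under their own guidelines. The semi-annual report on all adverse events also goes to the IND holder's IRB (13.8.2).
- *The size is 132 × 3 = 396 post-dose walks.* That counts walks in both arms (66 × 3 = 198 on sildenafil), not events. The protocol gives no event rate, so the product does not measure the problem.

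**Conclusion.** The point holds in limited form. For hypotension at a follow-up walk that needs admission, fluid resuscitation or a vasopressor, 13.7.1 and 13.7.2 give opposite IRB instructions with no rule of precedence. For fall injury and chest or extremity discomfort, the walk list exempts both grades, so its qualifiers do no work.

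The consequence is inconsistent or missing individual reports to local IRBs. No efficacy estimate or planned analysis is affected, and neither are the coordinating-center and DSMB routes. How many events are involved cannot be derived from the protocol. The peak-dose argument applies to the walks at weeks 6, 10 and 16. Appendix D sets the post-dose timing for all walk tests, but the screening and baseline walks precede randomized drug. This is an inexpensive safety-reporting correction worth making.

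**What to change.** Reconcile the two sections with two changes.

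1. State that 13.7.2 governs whenever an event meets an item in both lists. The vaso-occlusive exception already written into 13.7.2 stays.
2. Delete the three more severe walk items from the no-report list in 13.7.1. State that such events are reported under 13.7.2 when serious and otherwise according to each IRB's guidelines. The second half needs its own sentence, because the existing fallback in 13.7.2 covers serious events only.

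Moving all three items into 13.7.2 would go too far. That section is for serious events on 7- and 15-day deadlines, and treated discomfort or an evaluated fall need not be serious under section 13.2.2.

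The cost is protocol wording, matching consent text (both lists appear in the consent) and some additional IRB reports, whose number the protocol does not allow one to estimate. Only reporting changes; clinical care does not.
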